## Abstract

**Introduction:**

Diabetic ketoacidosis is one of the leading causes of unplanned hospital admission among people with diabetes, yet adherence to treatment guidelines remains inconsistent, contributing to variation in care and suboptimal outcomes. Conventional audit approaches are limited by non-standardised data collection, restricting benchmarking and shared learning. The Digital Evaluation of Ketosis and Other Diabetic Emergencies (DEKODE) platform was developed as a cloud-based audit-and-feedback system to support near real-time performance monitoring and continuous quality improvement, but its implementation requires theory-informed evaluation.

**Methods:**

This multi-site, mixed-methods study involves six National Health Service hospitals, including early adopters and sites new to DEKODE. Guided by an implementation research logic model, the study links contextual determinants to tailored strategies. Quantitative outcomes, including episode duration, guideline adherence, complications, and clinical outcomes, will be analysed using interrupted time series methods. Qualitative stakeholder interviews will be analysed thematically, and findings integrated using triangulation.

**Results:**

The study will assess the impact of DEKODE on clinical and process outcomes and identify determinants influencing adoption, fidelity, and sustainability.

**Discussion:**

Findings will inform scalable implementation of digital audit-and-feedback systems to reduce variation in acute diabetes care and improve patient outcomes.

**Clinical Trial Registration:**

https://www.isrctn.com/ISRCTN17096714, identifier ISRCTN17096714.

## Introduction

Diabetic ketoacidosis (DKA) is one of the leading causes of unplanned hospital admissions among people with diabetes and remains a major contributor to avoidable morbidity, mortality, and prolonged hospitalisation (1). Audits and quality improvement (QI) initiatives have been conducted in individual hospitals to evaluate and enhance DKA care (2, 3). Despite the availability of clear, evidence-based protocols in local, national, and international guidelines, adherence to recommendations remains inconsistent (4, 5). This inconsistency highlights a fundamental implementation challenge: the problem is not a lack of knowledge, but rather ensuring that effective care is delivered reliably, consistently, and sustainably in routine clinical practice (6). In implementation science, this is referred to as a knowledge translation gap (7).

A limitation of current improvement efforts is the lack of standardised data collection methods across sites (8, 9). Without consistent, comparable data, it is difficult to identify and disseminate best practices, benchmark performance, or support cross-institutional learning (10). Although various interventions—such as protocol updates, targeted education, and intermittent performance feedback—have shown short-term gains (11), improvements are rarely sustained (12). This underscores the need to apply theory-informed implementation approaches to understand the contextual factors that influence uptake, the mechanisms driving change, and the strategies required to sustain improvements over time (13). Without such approaches, interventions risk being fragmented, non-transferable, and vulnerable to decline once initial efforts subside.

To address these challenges, we developed the Digital Evaluation of Ketosis and Other Diabetic Emergencies (DEKODE) platform—a cloud-based audit and feedback (A&F) model designed to embed continuous quality improvement into the delivery of DKA care (14). DEKODE standardises data collection across hospitals, enables near real-time and longitudinal monitoring of process and outcome measures, provides quarterly performance feedback, and benchmarks institutional performance internally and externally (11). The design of DEKODE is adaptable to diverse healthcare settings, and can be embedded within existing hospital workflows, facilitating timely access to performance data for clinical teams and leadership (14). DEKODE enables rapid identification of care gaps, targeted interventions (14), and interactive refinements—such as monitoring for iatrogenic complications (14), increasing feedback frequency (11, 15), and integrating outcome-linked quality metrics (14).

Implementation of DEKODE has been guided by clinical performance feedback intervention theory (16). It began when a group of consultants and resident doctors, motivated to improve diabetic care, came together to initiate change. Since then, the program has relied on regular feedback on the clinical performance of individual hospitals compared with their baseline performance. The approach incorporates components identified in a 2025 update of a Cochrane review (17) as yielding the greatest A&F effect sizes through meta-regression:
providing data directly to individual hospitals rather than only at a group levelcomparing institutional performance against benchmarksusing interactive methods—such as regular meetings—rather than solely didactic or written formats to deliver feedbackapplying facilitation strategies to support engagementdeveloping action plans through agreements with local consultants to drive practice change within hospitalsThe DEKODE platform has also been successfully applied to other diabetic emergencies, including hyperosmolar hyperglycaemic state (HHS) and severe hypoglycaemia, demonstrating its adaptability and broader potential within acute diabetes care. These applications provide practical evidence that the model can be extended beyond DKA to other high-risk, time-sensitive conditions, supporting both local quality improvement and system-wide learning. Although informed by practical experience, DEKODE has not yet been rigorously evaluated within an implementation science framework.

This paper describes the design, implementation, and evaluation framework underpinning DEKODE, positioning it as a potentially scalable digital intervention for improving DKA care. The specific objectives for this implementation study are:
To identify and examine the facilitators and barriers to the set up, sustainability, and scalability of DEKODE using an evidence-informed implementation science framework.To evaluate how DEKODE contributes to improvements in DKA outcomes among existing and newly participating hospitals.Building on prior publications (14, 18) that have demonstrated DEKODE's utility, we now seek to situate it within an implementation science framework, specifically the Implementation Research Logic Model (IRLM). This work addresses an important gap in the literature by offering a theory-informed understanding of how improvements in DKA care can be achieved and sustained, while providing practical insights for scaling, adaptation, and replication across other acute care pathways.

## Methods

### Study design and setting

This multi-site, mixed-methods implementation study will be conducted within the Department of Applied Health Sciences at the University of Birmingham, with ethical approval obtained from the Health Research Authority (Ref: 25/IEC08/0011). The study protocol was registered with the ISRCTN registry (ISRCTN17096714; https://www.isrctn.com/ISRCTN17096714). The study will run from March 2026 to June 2028, preceded by a recruitment and onboarding phase starting in November 2025. Reporting of the study will adhere to the Standards for Reporting Implementation Studies (STaRI) checklist to ensure transparency, methodological rigour, and consistency in the dissemination of implementation research findings (Supplementary Material S1) (19).

### Patient and public involvement

Patient and public involvement activities were undertaken from the proposal design stage and will continue to inform dissemination plans. We consulted public members of the Joint British Diabetes Societies (JBDS) Patient Panel, the Diabetes UK Communities in Action group, and people with diabetes from the West Midlands region. These contributors also have links with national and international diabetes organisations, supporting the inclusion of wider patient perspectives relevant to diabetes care and policy.

The purpose of the consultation was to elicit the views of people with diabetes on the value of the study and to explore safety and ethical considerations associated with the proposed methods, particularly for work packages involving patients, carers, and healthcare professionals. Following an introductory discussion, a 30-minute Zoom meeting was held with two members of Diabetes UK Communities in Action. Feedback from this consultation supported the relevance of the study and informed the study design, qualitative interview approach, implementation evaluation, language refinement, and dissemination plans.

### Implementation science framework

Earlier evaluations demonstrated DEKODE's feasibility and potential to improve DKA outcomes (14); However, uptake has varied considerably across hospitals, with some sites integrating DEKODE into routine workflows more rapidly than others. A key limitation has been inconsistent clinician engagement (20, 21), with some perceiving performance feedback as a threat to professional identity rather than an opportunity for improvement (22). Such challenges underscore the importance of addressing the relational and cultural dimensions of implementation alongside technical aspects. We recognise that knowledge context–strategy–mechanism relationships, as articulated in the IRLM framework, will be central to supporting sustainability and scalability in the next phase of work (23).

To address the existing variations, we have chosen the IRLM as the overarching framework for the study's design, data collection, analysis, and interpretation (24).

Implementation research often draws on multiple frameworks to address determinants, processes, and evaluation, but integrating this led to fragmented strategies and conceptual ambiguity (25). The IRLM mitigates this challenge by providing a single, integrative structure that explicitly links contextual determinants, implementation strategies, mechanisms of action, and both implementation and clinical outcomes (25).

IRLM enables the consolidation of complementary frameworks–such as the Consolidated Framework for Implementation Research (CFIR), Reach, Effectiveness, Adoption, Implementation, and Maintenance (RE-AIM), and Theoretical Domains Framework (TDF) while maintaining conceptual clarity (24), rather than using each framework individually, which can result in omission of important information. It has been successfully applied across various healthcare settings (26–28). A national evaluation of IRLM utility found that over 50% of respondents rated it as “moderately” or “very helpful” for usability, conceptual clarity, and applicability to real-world challenges (29). Its graphic depiction further facilitates transparency, stakeholder communication, and reproducibility, which are valuable for multisite digital interventions such as DEKODE (24).

The IRLM serves as the overarching framework for this study by providing a structured representation of the relationships between implementation determinants, strategies, mechanisms, and outcomes. Within the IRLM, the CFIR is used to identify and categorise contextual determinants that may influence DEKODE implementation, including factors related to the intervention itself, organisational context, individual users, and implementation processes. These determinants are then linked to implementation strategies using the Expert Recommendations for Implementing Change (ERIC) taxonomy (30), which provides a comprehensive set of evidence-informed strategies to address identified barriers and strengthen facilitators. CFIR informs what implementation challenges exist, ERIC informs how those challenges may be addressed, and the IRLM integrates these relationships into a coherent causal pathway linking DEKODE implementation activities to mechanisms of changes, implementation outcomes, and clinical outcomes. We have hypothesised mechanisms of action through which selected strategies are expected to enhance fidelity, adoption, and sustainability, ultimately leading to improved patient outcomes through the improvement management of DKA. This information is mapped in our adapted IRLM (Figure 1).

**Figure 1 F1:**
[figure not shown]
Adapted IRLM for the DEKODE initiative. The IRLM illustrates the overarching structure linking implementation determinants, strategies, mechanisms, and outcomes underpinning the DEKODE implementation approach. Determinants were identified using the CFIR and mapped across the five IRLM domains: Intervention Characteristics, Outer Setting, Inner Setting, Characteristics of Individuals, and Process. Implementation strategies were selected and operationalised using the ERIC taxonomy to address identified barriers and leverage facilitators. These strategies are hypothesised to act through mechanisms such as increasing knowledge, engagement, confidence, peer learning, and organisational support, leading to improved implementation outcomes (adoption, fidelity, penetration, sustainability, feasibility) and ultimately improved clinical outcomes in DKA care.

### Site selection and sample size rationale

We will purposely select six National Health Service (NHS) hospitals across England to participate in the study. All centres who have been using the DEKODE platform for at least twelve months will be invited to participate in this research. From this, three centres who are interested to participate in the study following informed consent will be included on a first come basis. Similar, all new interested in joining the DEKODE surveillance system will be invited to participate in the study as well. The three centres interested to participate after informed consent will be included in the study on a first come basis as well. This sampling strategy is designed to capture implementation processes across sites with varying levels of experience, organisational structures, resources, and clinical workflows. This approach balances practical feasibility of delivering the evaluation with the need to explore variability, enhancing the transferability of findings to broader NHS settings.

The number of participating centres was selected pragmatically to balance feasibility with the need to capture variation in organisational context, clinical workflow, and implementation maturity. The inclusion of three early adopter sites is informed by previous DEKODE work, in which data from 177 DKA episodes across three hospitals were used to evaluate variation in DKA care processes, examine factors influencing length of stay and test quality improvement interventions. Although that study did not demonstrate a significant reduction in. DKA duration or length of stay, it demonstrated the feasibility of using a three-hospital DEKODE dataset to support multi-side audit, benchmarking, and quality improvement. The present study expands this approach by including three early adopter sites and three new implementer sites, enabling comparison across different levels of implementation maturity and hospital context. For the quantitative component, all eligible adult DKA episodes identified during the baseline, implementation, and follow-up periods will be included, with the final number determined by site-level DKA admission volumes.

### Eligibility criteria and case definition

Eligible episodes will include adults aged ≥16 years who are admitted with DKA or who develop DKA during hospital admission at a participating centre during the study period. All types of diabetes will be eligible, provided that the episode meets the diagnostic criteria for DKA according to the Joint British Diabetes Societies (JBDS) DKA guideline.

In line with the JBDS DKA guideline, DKA will be defined by the presence of hyperglycaemia or known diabetes, ketonaemia or significant ketonuria, and metabolic acidosis. This will generally include capillary or blood ketones ≥3.0 mmol/L or significant ketonuria, venous or arterial pH <7.3 and/ or serum bicarbonate <15 mmol/L, alongside clinical assessment consistent with DKA.

Each DKA presentation will be treated as a separate episode for audit and feedback purposes. Recurrent DKA admissions in the same individual will therefore be included as separate episodes, as each presentation represents a distinct episode of care and an opportunity to evaluate DKA management.

Episodes will be excluded if the JBDS diagnostic criteria for DKA are not met, if the presentation represents isolated ketosis without acidosis, hyperosmolar hyperglycaemia state without DKA, or if essential data required to confirm DKA diagnosis are unavailable.

### DEKODE implementation process

Interested participating hospitals will be provided with access to an online study folder containing the study protocol and data collection form, which will support local audit registration. Following local registration, each site will share its audit registration number with the central DEKODE team and attend a virtual onboarding meeting covering the study protocol, eligibility criteria, and data collection procedures.

Each participating site will identify a local centre lead, who will coordinate communication between the local team and the central DEKODE team. Data collection will primarily be undertaken by clinicians and medical students involved in the DEKODE project, following audit registration and training. Local audit, governance, and quality improvement structures will be engaged to support approval, oversight, and alignment of the initiative with existing hospital processes.

Implementation will involve site onboarding, local audit registration, training of local data collectors and clinical leads, standardised data collection through REDCap-based DEKODE platform, quarterly audit-and-feedback reports, and structured local action planning. Each hospital will obtain a patient list from its information team for adults aged ≥16 years who were admitted with DKA or developed DKA during admission. Patient-identifiable data will remain within the local hospital team and will not be shared with the central DEODE team. The central team will receive only pseudonymised data through REDCap.

Standardisation across participating sites will be supported through use of common study protocol, eligibility criteria, data collection form, data dictionary, and REDCap-based data submission platform. All sites will collect the same core dataset for each eligible DKA episode, including diagnostic criteria, key timestamps, biochemical monitoring, treatment processes, complications, and clinical outcomes. The virtual onboarding meeting and pilot review of five DKA episodes will be used to ensure that local data collectors interpret variables consistently before full data collection begins. This approach is intended to support comparable data collection, benchmarking, and cross-site learning while allowing local adaptation in how improvement actions are implemented.

Although data collection will be led by the local DEKODE team, the quarterly feedback reports may identify care gaps that require wider multidisciplinary input. Depending on local findings, improvement actions may involve diabetes and endocrinology clinicians, acute medicine and emergency department teams, nursing staff, pharmacy, dietetics or nutrition teams, information or digital teams, patient safety teams, and operational leadership. This approach ensures that DEKODE remains operationally feasible as a clinician-led audit-and-feedback programme, while allowing wider multidisciplinary engagement when specific improvement interventions require it.

To ensure data quality, each site will initially submit five pilot DKA episodes for central review. The DEKODE team will assess data completeness, accuracy and consistency, and provide feedback before full data collection continues for the agreed study period. Submitted data will then be monitored for completeness, consistency and plausibility, with queries returned to the local centre lead for clarification or correction using local source records where required.

Participating hospitals will receive feedback reports every three months, summarising local processes and outcome measures. Local teams will use these reports to identify gaps in DKA care and decide on appropriate context-specific improvement interventions. In addition, monthly meetings will be held with all participating centres to discuss progress, share learning, address challenges, and support consistency across sites. A virtual group communication channel will also be established to enable real-time communication between participating centres and the central DEKODE team. This will allow implementation issues, data collection queries, and site-specific challenges to be identified promptly and addressed iteratively.

Implementation fidelity will be monitored by assessing whether core DEKODE components are delivered as intended, including local audit registration, completion of onboarding, submission of pseudonymised data, pilot data review, quarterly feedback reporting, and participation in ongoing communication or feedback processes. Local adaptations and implementation challenges will be documented to distinguish necessary contextual tailoring from deviation from core intervention components. These implementation tools and strategies will operationalise the IRLM, CFIR, and ERIC-informed approach by linking identified contextual barriers to practical actions, feedback mechanisms, local adaptations, and follow-up improvement planning at each participating site.

### Quantitative data collection and outcomes

The study will include a six-month baseline period prior to DEKODE implementation or evaluation (January to June 2026), a six-month active implementation phase (July to December 2026), and a twelve-month follow-up period (January to December 2027). This proposed timeline is informed by previous DEKODE evaluations, in which improvements in DKA care episode duration were detectable within a comparable follow-up period after implementation (11). An interrupted time series (ITS) design will be applied to assess changes in outcomes attributable to DEKODE implementation.

The primary quantitative outcomes include the DKA episode duration, defined as the time from diagnosis to biochemical resolution; adherence to the Joint British Diabetes Societies (JDBS) guidelines for DKA between 80% and 120% of the recommendations, such as timely initiation of insulin treatment, adequate fluid resuscitation, and appropriate biochemical monitoring; and the occurrence of iatrogenic complications, including hypokalaemia and hypoglycaemia. In addition, we will assess key clinical outcomes, namely in-hospital mortality, 30-day readmission rates for DKA, and overall length of hospital stay. Secondary outcomes will focus on comparative performance between early adopter and new implementer sites, as well as site-level variation relative to the collective dataset, enabling benchmarking across participating hospitals.

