Interviews will take place twice during the study, each involving a distinct cohort of participants: first, within six to nine months after DEKODE activation to capture initial implementation experiences, and later near the end of the study period to assess sustained engagement, perceived benefits, and any ongoing barriers or facilitators. The interview guides will be piloted and refined at an initial site before use across all participating centres. All interviews will be audio-recorded, transcribed verbatim, and pseudoanonymised to protect participant confidentiality.

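### Three of the six sites will already be using DEKODE throughout the January–June 2026 baseline, so a July 2026 interruption there cannot identify an implementation effect, and the ITS is not limited to the new sites

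*Protocol article*

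**What the plan says.** **Sites** (Site selection and sample size rationale). "We will purposely select six National Health Service (NHS) hospitals across England to participate in the study". Half are existing users: "All centres who have been using the DEKODE platform for at least twelve months will be invited to participate in this research", and "From this, three centres who are interested to participate in the study following informed consent will be included on a first come basis". The other three are centres new to the platform. The section describes the design as "including three early adopter sites and three new implementer sites, enabling comparison across different levels of implementation maturity and hospital context".

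**Calendar** (Quantitative data collection and outcomes). "The study will include a six-month baseline period prior to DEKODE implementation or evaluation (January to June 2026". Active implementation follows from July to December 2026, and follow-up runs from January to December 2027. These dates are given once, for the study as a whole. Study design and setting puts the start of recruitment and onboarding in November 2025 and the start of the study in March 2026.

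**Analysis** (same section). "An interrupted time series (ITS) design will be applied to assess changes in outcomes attributable to DEKODE implementation". No site group is named. The comparison of early adopters with new implementers is listed among the secondary outcomes. The second study objective, in the Introduction, covers existing as well as newly participating hospitals.

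**Interviews** (Survey and qualitative interviews). The first wave is timed "first, within six to nine months after DEKODE activation to capture initial implementation experiences".

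**The concern.** An ITS identifies an intervention effect by projecting a pre-intervention segment forward and comparing it with what follows. The article calls January–June 2026 that segment, but its own entry rule makes those months post-intervention at half the sites. The wording of the baseline sentence, which lets the period precede either implementation or evaluation, appears to acknowledge this. The aim two sentences later is nevertheless change attributable to implementation, with no separate interruption date or earlier baseline for the existing users.

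Two errors of interpretation are at stake. If the early adopters' series is read on its own, a shift in July 2026 could be credited to introducing DEKODE when DEKODE was introduced there earlier. If the early adopters enter a common series with the new sites, a real effect at the new sites could be diluted, and a weak or null result read as DEKODE not working.

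**Working it through.** The article gives no effect size, power or target number for the ITS, so there is no stated figure to reproduce. The check has three parts.

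**1. Is the early adopters' baseline exposed?** The entry rule is at least 12 months of use, but the article does not say at which date this is counted. Each plausible date gives:

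| 12 months counted back from | Use began no later than | Baseline months exposed |
|---|---|---|
| November 2025 (recruitment opens) | November 2024 | 6 of 6 |
| March 2026 (study start) | March 2025 | 6 of 6 |
| July 2026 (active implementation starts) | July 2025 | 6 of 6 |

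On every reading, use precedes January 2026. This applies to 3 of 6 sites (50%).

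**2. What would a common six-site series estimate?** Assumptions, none of them in the article:

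- the true level change at the new sites in July 2026 is δ;
- the early adopters reached their change before January 2026 and do not change further;
- the early adopters supply share s of episodes in every month;
- all six sites form one series with one July 2026 interruption.

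The pooled level change is then s × 0 + (1−s) × δ = (1−s)δ.

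This was checked by a noise-free segmented regression on 24 monthly points (6 baseline, 18 later), with intercept, trend, level change and slope change at July 2026. The new sites went from 10 to 9 (δ = −1) and the early adopters were flat at 9:

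| s | Pooled level change | New sites alone | Early adopters alone |
|---|---|---|---|
| 0.3 | −0.70 | −1.00 | 0.00 |
| 0.4 | −0.60 | −1.00 | 0.00 |
| 0.5 | −0.50 | −1.00 | 0.00 |
| 0.6 | −0.40 | −1.00 | 0.00 |
| 0.7 | −0.30 | −1.00 | 0.00 |

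Modelling the groups separately recovers the full effect at the new sites and shows no first-implementation effect at the early adopters.

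**3. What does restricting to the new sites cost in precision?** If episodes are independent with equal variance, the standard error scales with 1/√N. Keeping the fraction (1−s) of episodes multiplies it by 1/√(1−s), which at s = 0.5 is 1/√0.5 = 1.41. Under the assumptions of part 2 the target rises from (1−s)δ to δ, a factor of 1/(1−s) = 2 at s = 0.5. The ratio of effect to standard error therefore changes by 2/1.41 = 1.41 in favour of the restricted analysis. The interval is wider, but it is centred on the right quantity.

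**The case against.** The strongest reply is that the article never says the six sites form one series. It says only that an ITS will be applied, and model structure is commonly left to an analysis plan, which is not shown. The article also plans to compare early adopters with new implementers and to examine site-level variation, so it does not treat the sites as interchangeable. This stands: pooling is an inference from the single calendar and the unrestricted ITS sentence, and the dilution figures depend on it. It does not remove the main point. The entry rule, the baseline window and the aim are all fixed in the article, and no analysis plan can make exposed months unexposed.

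Some stronger readings are tempting but not supported:

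- *Nothing changes at the early adopters in July 2026.* DEKODE implementation process describes monthly meetings with all participating centres and a communication channel still to be set up. Some study activity may be new there, though the Introduction suggests that parts of it already existed. A July 2026 shift is therefore not necessarily secular change; it is just not first implementation.
- *The second objective cannot be answered.* The three new sites can still support an ITS with the data already planned.
- *Early adopters are a ready-made control, with bias only towards caution.* They are already treated. Added study activity there would shrink the contrast, while fading of their earlier effect, a possibility raised in Strengths and limitations, would inflate it.
- *A pre-go-live baseline exists for the early adopters.* The Introduction mentions "regular feedback on the clinical performance of individual hospitals compared with their baseline performance", but does not say that this baseline predates go-live or that it forms a usable time series.
- *The first interview window has already passed at these sites.* That depends on what activation means, which the article does not define.

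**Conclusion.** The point holds in this form. At three of six sites the whole January–June 2026 baseline is exposed time, and this follows from the article's own entry rule and dates without further assumption. For those sites a July 2026 interruption cannot identify change attributable to DEKODE implementation, and the article does not limit the ITS to the sites where it can.

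The size is conditional. If all six sites share one series and the early adopters do not change further, the estimate is 0.7 to 0.3 of the new-site effect for s from 0.3 to 0.7, and half at s = 0.5. The share s is an assumption, because site volumes are not given. A fading or still-growing earlier effect, or a response to new study activity, would change the size of the bias but would not make the baseline unexposed. If the groups are analysed separately there is no dilution; the mislabelled baseline at the early adopters remains.

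**What to change.** 1. State that the implementation effect is estimated by ITS in the three new-implementer sites only.
2. Analyse the three early adopters as a separate series, labelled maintenance or the effect of study participation, not implementation. Reword the baseline sentence to say what the period is for each group.
3. If new sites are contrasted with early adopters over time to estimate the effect, make it a sensitivity analysis only. State that the comparison sites are already treated and that the bias can go either way.
4. Use an ITS at an early adopter's own go-live date only if an adequate pre-go-live series is shown to exist for that site.
5. Define DEKODE activation for the early adopters' first interview wave. If it means first go-live, the six-to-nine-month window has passed; tie that wave to a calendar window and label it maintenance.

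The cost is wording in the protocol and analysis plan, with no new patients or data items. The downside is that the effect estimate rests on three sites and is less precise: at s = 0.5 its standard error is about 1.41 times that of a six-site analysis, under the simple assumptions shown above.
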